### Study integrity, trial design, and procedure

The present study received ethical approval from the La Trobe University Human Research Ethics Committee (HEC016-10), and the trial was registered with the Australian New Zealand Clinical Trials Registry (ACTRN12616001018404). The present RCT adheres to the CONsolidated Standards Of Reporting Trials (CONSORT). The intervention protocol for both conditions will be manualized, and sessions with therapists for both conditions will be audio-recorded to enable quality assurance and assessment of protocol adherence.

The design will be a RCT involving 50 young adults, recruited over a five-month period (10 participants per month). This sample size was calculated using G*Power software to enable sufficient assessment of change over time in the study outcome measures. To assess change across three time points and between two conditions in a mixed-design ANOVA with both within (time) and between (condition) subjects effects, a sample of 42 is needed to detect a small-medium effect size of *f* = .20 at power = .80 and alpha = .05. Therefore, a sample of 50 will provide sufficient power while also accounting for possible attrition. Analyses will be conducted on an intention to treat basis.

Informed consent will be obtained prior to each participant commencing the study. Following initial screening described above, a research assistant will provide each participant with a pre-intervention questionnaire which will assess the primary and secondary outcome measures described below. Following completion of the pre-intervention questionnaire, participants will be randomly assigned to either the CFT or CBT condition with simple randomization using a computerized random number generator, and will be provided with the respective guidebooks. A therapist will contact participants approximately 1 week later to schedule session appointments. Participants will complete their respective intervention across an 8-week period. One-week post-intervention, a research assistant will provide each participant with a post-intervention questionnaire, which will again assess the primary and secondary outcome measures described below, as well as consumer satisfaction. Three-months post-intervention, the research assistant will provide participants with the follow-up questionnaire containing the primary and secondary outcome measures.

### Intervention procedures and delivery

Manualized treatment protocols have been developed for both the CFT and CBT interventions. Both interventions involve self-guided reading and activities, and some contact with a therapist via Skype, which will allow for people across the country to participate in the intervention. It will also test the intervention in a flexible delivery format to potentially enhance reach to LGB young adults who face barriers accessing face-to-face services [15, 16].

The CFT program is an 8-week compassionate mind training intervention (compassion-focused therapy) adapted to be appropriate for LGB young adults, and tailored to their unique life experiences. It consists of 8-units, each incorporating self-directed reading and experiential activities, coupled with weekly Skype sessions with a trained therapist to ensure compliance and to assist with tailoring skills to the specific individual’s situation. The eight units cover 1) psychoeducation pertaining to compassion, evolution, life challenges, brain functioning, and emotion systems to enhance understanding of the evolved functions that underpin emotions and behavior, and to facilitate de-shaming; 2) body-focused interventions (e.g., body posture, soothing rhythm breathing, voice tone exercises) to facilitate affiliative processing and the activation of the parasympathetic system, a core process in emotion regulation and mentalization (empathy/perspective taking); 3) cultivation of mindful attention, including non-judgmental awareness of experiences; 4) cultivation of the compassionate self as the persons motivational system through imagery practices. This also includes addressing the fears, blocks and resistances to compassion. Each of the units are tailored to cultivate the compassionate self, which is an orientation of the mind aimed at creating an inner secure base/safe haven for the individual to address and reduce shame and internalized stigma, and alleviate depression.

The units involve evidence-based step-by-step training founded on mindfulness and compassion-focused principles [20] and include examples relating to the lives of young LGB adults. For instance, included within the protocol is content pertaining to stigma and discrimination, significant life events such as coming out, and the effects of internalized homophobia and shame. These experiences of shame and internalized stigma are discussed in the context of negative societal attitudes to facilitate de-blaming and reduce shame. Specific exercises are included for participants to apply compassion-focused strategies to their own situation, with audio recordings of each exercise to facilitate practice between sessions.

Participants assigned to the CBT condition will receive a hard copy of an evidence-based cognitive-behavioral self-help book *Feeling Good: The New Mood Therapy* [30]. This cognitive behavioral bibliotherapy program guides the reader through a series of sections that provide psychoeducation about their symptoms of depression, and a series of self-directed cognitive and behavioral exercises to complete. This book has been established as beneficial for depression [31]. Participants will be provided with a guide to which sections of the book to read across the eight-week program. At the mid-point of this program (week 4), each participant will have a 1-hour telephone or Skype session with a therapist to monitor compliance, assist with any questions, and troubleshoot any difficulties with the exercises.

### Measures

#### Primary outcome

The primary outcomes will be depressive symptomatology, assessed by the Beck Depression Inventory-II (BDI-II) [28]. The BDI-II is a widely used 21-item self-report measure of depressive symptomatology which requires participants to respond to statements describing symptoms of depression on a scale from 0 (*never*) to 3 (*always*). The BDI-II specifies symptom severity from non-clinical to clinical ranges, and has demonstrated sound reliability and validity [32, 33].

#### Secondary outcomes

We also included several secondary outcome measures to assess whether the intervention is associated with a reduction in symptoms commonly associated with depression, including anxiety [34] and suicidal ideation [29]. In addition, we included secondary outcome measures associated with the targets of the CFT intervention described earlier, including internalized stigma [35], self-compassion [36] and shame [37].

The Beck Anxiety Inventory (BAI) [34] will be used to measure symptoms of anxiety. The BAI is a 21-item self-report measure of symptoms of anxiety, and demonstrates excellent validity, internal consistency, and test-retest reliability [34, 38]. The BAI asks participants to respond to a series of questions pertaining to symptoms of anxiety on a 4-point scale, ranging from 0 (*never*) to 3 (*always*).

The Suicide Behaviors Questionnaire-Revised [29] is a widely used 4-item self-report measure to assess suicidal ideation. The SBQ-R is a valid and reliable measure of suicidal ideation [29, 39], and effectively discriminates between non-suicidal and suicidal individuals [29].

The Lesbian, Gay, and Bisexual Identity Scale (LGBIS) [35] is a 27-item self-report measure that assesses eight minority stress-related constructs that each form eight subscales. Three subscales will be used in this research, which assess internalized stigma (Internalized Homonegativity subscale), motivations to conceal one’s sexual identity (Concealment Motivation subscale), and feeling positive about being LGB (Identity Affirmation subscale). The scale is measured on a 6-point Likert scale, ranging from 1 (*disagree strongly*) to 6 (*agree strongly*). The measure has demonstrable construct validity and internal consistency [35, 40].

The Self-Compassion Scale – Short Form [36] is a widely used 12-item measure of an individual’s capacity to experience feelings of kindness towards themselves, and to hold difficult feelings with warmth and concern as opposed to self-criticism. The 12 items are rated on a 5-point scale ranging from 1 (*almost never*) to 5 (*almost always*), and the measure has excellent psychometric properties, including validity and reliability [36].

The Guilt and Shame Proneness Scale [37] is a 16-item self-report measure of an individual’s feelings of shame and guilt. This will be included to assess shame and guilt proneness at a broad level, beyond sexual orientation. Participants respond to the items on a 7-point scale ranging from 0 (*unlikely*) to 4 (*very likely*). The measure is a valid and reliable measure of guilt and shame proneness, and demonstrates high test-retest reliability [37].

Finally, three measures to examine consumer satisfaction and acceptability will be included. The Consumer Satisfaction Questionnaire [41] is a widely used measure that assesses the helpfulness of an intervention or service. The LGBT Appropriateness Scale [18] is a 12-item measure of the extent to which LGB individuals perceive an intervention inclusive and relevant to them. Participants indicate whether they agree or disagree with the 12 statements pertaining to the suitability of the program for LGB individuals. Finally, participants in the CFT condition will rate the extent to which each of the eight core compassion-focused skills were helpful on a 5-point scale, ranging from 1 (*not at all helpful*) to 5 (*extremely helpful*).

### Statistical analyses

This RCT is a mixed-model repeated measures design involving between- and within-participants factors. The between-participants factor, or independent variable, is condition (CFT vs CBT). The within-participants factor is assessment time, with each participant assessed on relevant primary and secondary outcome measures at three time points (pre- and post-intervention, plus 3-month follow-up). A mixed-model repeated measures analysis of variance (ANOVA) will assess main and interaction effects across the three time points and between the two conditions. Participants in both conditions will also complete the BDI at each session with the therapist (sessions 1–8 for those in the CFT condition, at session 4 for those in the control). Should any participant not complete the post-questionnaire, their most recent BDI score will be used in order to maximize all available data. The effect size (Cohen’s *d*) and its precision will be calculated with 95% CI for the mean differences between pre-, post-, and follow-up for each condition.

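### The ANOVA treats the pre-randomisation BDI-II as an outcome level: its 2-df interaction test is valid and correctly sized, but less efficient and less direct than a pre-specified baseline-adjusted contrast

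*Protocol article*

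**What the plan says.** The primary outcome is the BDI-II. Under Statistical analyses, the between-participants factor is condition (CFT or CBT) and time is the within-participants factor: "The within-participants factor is assessment time, with each participant assessed on relevant primary and secondary outcome measures at three time points", namely pre-intervention, post-intervention and 3-month follow-up. A mixed repeated-measures ANOVA "will assess main and interaction effects across the three time points and between the two conditions". The article names no baseline covariate, no single contrast and no primary time point.

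Under Study integrity, trial design, and procedure, the order of events is explicit: "Following completion of the pre-intervention questionnaire, participants will be randomly assigned to either the CFT or CBT condition". The same section sizes the trial on this ANOVA. It says "a sample of 42 is needed to detect a small-medium effect size" of f = .20 at power .80 and alpha .05, and plans 50 to allow for attrition.

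The Study objectives and hypotheses section predicts lower depressive symptoms in CFT than in CBT at both post-intervention and 3 months, relative to baseline.

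**The concern.** A score taken before randomisation cannot carry a treatment effect; the arms differ on it only by chance. Used as one of three outcome levels, it enters the comparison of conditions with a fixed weight instead of a weight estimated by regression, so less of the between-person variation is removed than the data allow.

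The interaction also has 2 df. It asks whether the two profiles depart from parallel in any way, whereas the hypothesis is directional and names two visits. A significant interaction would not by itself say at which visit the arms differ, or in whose favour. The other between-condition test, the condition main effect, averages in the pre-randomisation score and so dilutes any effect. What is at stake is precision and a clear answer in a trial of 50 people.

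**Working it through.** **Inputs.** From the article: 2 conditions, 3 times, f = .20, alpha .05, power .80, N = 42 required and 50 planned. Assumed, because the article does not state them: correlation rho = .5 between any two visits (range .3 to .7 shown), compound symmetry with sphericity, equal arms, SD = 1.

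**Step 1. Reproduce the stated N.** For the condition-by-time interaction, lambda = f² × N × 3 / (1 − rho), with df 2 and 2(N − 2).
- N = 42, rho = .5: lambda = 0.04 × 42 × 3 / 0.5 = 10.08, df 2 and 80, power 0.803. The smallest even N that reaches .80 is 42, which matches the plan.
- The time main effect also gives 42, but it does not compare conditions.
- The condition main effect at f = .20 would need 134, so the trial was not sized on it.

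**Step 2. Translate f = .20 into the hypothesised pattern.** Take a difference between arms of 0 at baseline and d at both later visits. The interaction deviations per arm are ±d/3, ±d/6 and ±d/6. Their mean square is d²(1/9 + 1/36 + 1/36)/3 = d²/18. So f = d/√18, and f = .20 means d = 0.20 × 4.243 = 0.85 SD.

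**Step 3. Power of 1-df contrasts at that effect.** lambda = d² × N / (4v), with d² = 0.72. The variance factor v and the error df are:
- adjusted post: v = 1 − rho², df N − 3
- adjusted average of post and 3 months: v = (1 + rho)/2 − rho², df N − 3
- unadjusted average minus baseline: v = 1.5(1 − rho), df N − 2
- unadjusted post minus baseline: v = 2(1 − rho), df N − 2

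At N = 42 and rho = .5:
- adjusted post: v = 0.75, lambda = 0.72 × 42 / 3 = 10.08, power 0.872
- adjusted average: v = 0.50, lambda = 0.72 × 42 / 2 = 15.12, power 0.966
- unadjusted average change: v = 0.75, lambda = 10.08, power 0.872
- unadjusted post change: v = 1.00, lambda = 7.56, power 0.765

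| N | rho | Interaction (2 df) | Adjusted post | Adjusted average |
|---|---|---|---|---|
| 42 | .3 | 0.65 | 0.80 | 0.95 |
| 42 | .5 | 0.80 | 0.87 | 0.97 |
| 42 | .7 | 0.96 | 0.96 | 0.99 |
| 50 | .5 | 0.87 | 0.92 | 0.99 |

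The N for 80% power at rho = .5 is 42, 36 and 24 respectively. A simulation of 20,000 trials at N = 42, rho = .5 gave 0.808, 0.860 and 0.964, with type I error between 0.050 and 0.053 for all three tests.

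**Step 4. Dependence on the pattern (N = 42, rho = .5, d = 0.85).** If the effect exists at post only, the interaction still has 0.803 and the adjusted post contrast 0.872, but the adjusted average drops to 0.475. If it exists at 3 months only, a post contrast has no power beyond 0.05.

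**Step 5. The condition main effect.** Under the sustained pattern at N = 42 and rho = .5 its power is 0.59.

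**The case against.** The planned analysis is conventional, internally consistent and correctly sized. The interaction holds its 5% error rate, and the design and analysis sections agree with each other. A reader might infer that the plan is wrong or that the trial is underpowered. The documents do not support that: on its own terms the planned test has 0.80 power at 42 and 0.87 at 50. This objection stands, and the point is one of efficiency and directness only.

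The gain also depends on the contrast. Part of the advantage of the averaged contrast comes from pooling two visits in a 1-df test: without any covariate that already gives 0.87. The rest, up to 0.97, is the baseline adjustment. The averaged contrast loses to the interaction if the effect is at post only, a case the omnibus test guards against. At rho = .7 the adjusted post contrast gains less than one point (0.959 against 0.964). All of this stands and is built into the recommendation.

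Two further inferences should be resisted. One is that simple randomisation makes baseline imbalance especially likely. Simple randomisation mainly affects arm sizes; chance imbalance on BDI-II would be much the same under blocking not stratified on it. The other is that reliance on sphericity is a defect of the article. A correction for it is the kind of detail an analysis plan supplies.

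A separate analysis plan might also name contrasts. Even so, the article itself fixes the pre-intervention score as an outcome level and sizes the trial on that model.

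**Conclusion.** The point holds as a recommended improvement; it is not an error in the plan. At the design effect (0.85 SD at both later visits, compound symmetry, rho = .5), the 2-df interaction gives up about 7 points of power against the adjusted post contrast and 16 against the adjusted average at N = 42, and about 5 and 11 points at N = 50. Across rho .3 to .7 at N = 42, the shortfall against the adjusted post contrast runs from 15 points to almost none, and against the adjusted average from about 30 points to about 4. The figures for the average require a sustained effect, which is what the hypothesis predicts but the trial cannot guarantee. Apart from power, a named contrast would answer the stated hypothesis directly, which the omnibus interaction does not.

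**What to change.** Model post-intervention and 3-month BDI-II as the outcomes, with condition, visit, condition-by-visit, baseline BDI-II and baseline-by-visit. A constrained longitudinal model with a common baseline mean is an acceptable alternative.

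Name one primary condition contrast before the data are seen: either the difference at post-intervention, or the average over post and 3 months if a sustained effect is expected. Report both visit-specific differences in either case. Use the same form for each secondary outcome, with that outcome's own baseline.

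The cost is small. The baseline is already collected from every participant before randomisation. The sample-size sentence, now written for the mixed ANOVA, needs rewording to refer to the chosen contrast and to state the assumed correlation. N does not change.

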**Methods:**

The CFT intervention consists of 8 units with self-directed reading and activities tailored to LGB young adults, and 8 x weekly 1-hour consultations with a therapist. The CBT intervention consists of 8 units with self-guided reading and activities, with 1 x 1-hour session with a therapist at the mid-point of therapy. Fifty LGB individuals with scores of 13 or above on the Beck Depression Inventory-II will be randomized to either the CFT or CBT condition. The primary outcome measure is depressive symptomatology. Secondary outcome measures are symptoms of anxiety, suicidal ideation, internalized homophobia, self-compassion, and shame and guilt proneness. Assessments will occur at pre-intervention, post-intervention, and at 3-month post-intervention.

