### Study objectives and hypotheses

The present RCT will test the preliminary efficacy of a newly developed tailored CFT intervention specifically designed to meet the needs of LGB young adults compared to a standard untailored CBT intervention. The aim is to assess whether a CFT intervention specifically tailored for LGB young adults will reduce depressive symptomatology and shame, and improve psychological functioning.

With regards to the primary outcome, it is hypothesized that, compared to the CBT condition, those in the CFT condition will demonstrate significantly lower symptoms of depression at post-intervention and 3-month follow-up compared to baseline pre-intervention levels. With regard to secondary outcomes, it is hypothesized that compared to those in the CBT condition, those in the CFT condition will demonstrate significantly lower symptoms of anxiety, suicidal ideation, internalized homophobia, and shame and guilt proneness, and significantly higher scores on a measure of self-compassion at post-intervention and 3-month follow-up compared to baseline levels.

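### Missing post-treatment BDI-II scores are filled from as late as week 8 in CFT but no later than week 4 in CBT, so the primary comparison carries a bias whose sign depends on dropout

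*Protocol article*

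**What the plan says.** The rule is in the protocol article, Statistical analyses: "Should any participant not complete the post-questionnaire, their most recent BDI score will be used in order to maximize all available data". The sentence before it gives the source of those scores, namely BDI completion at therapist sessions: "sessions 1–8 for those in the CFT condition, at session 4 for those in the control".

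The schedule is consistent elsewhere. The Methods part of the abstract gives CFT "8 x weekly 1-hour consultations with a therapist". For CBT, Intervention procedures and delivery says: "At the mid-point of this program (week 4), each participant will have a 1-hour telephone or Skype session with a therapist". The section on study integrity, trial design and procedure sets an 8-week programme and then states: "One-week post-intervention, a research assistant will provide each participant with a post-intervention questionnaire". That section also commits to intention-to-treat analysis.

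The BDI-II is the primary outcome. The hypothesis is a contrast with CBT, in which "those in the CFT condition will demonstrate significantly lower symptoms of depression at post-intervention and 3-month follow-up compared to baseline pre-intervention levels". The analysis is described as follows: "A mixed-model repeated measures analysis of variance (ANOVA) will assess main and interaction effects across the three time points and between the two conditions".

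The replacement rule covers the post-intervention questionnaire only; none is stated for the 3-month score. The limitations in the Discussion do not mention the unequal BDI schedule.

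**The concern.** This is last observation carried forward on the primary outcome, with a source that differs by arm. Depression scores are expected to fall in both arms: the article describes the CBT book as of established benefit. When scores are falling, an older value is a higher value. A CBT participant without a post score is frozen at week 4, or at baseline if the one session was missed. A CFT participant who attended to the end is frozen one week before the assessment.

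The arms can then differ at post-treatment only because one was measured more often. Since the hypothesis is a between-arm contrast, this is bias in the quantity of interest and not just lost precision. The filled-in value is also analysed as if observed, which ignores the uncertainty of imputing it.

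**Working it through.** **Inputs from the article.** CFT sessions 1–8, weekly; one CBT session, week 4; post assessment one week after an 8-week programme, so week 9; 50 randomised against 42 required.

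**Inputs assumed, because the article gives none.** Session k falls in week k. True arm difference 0. Linear 10-point fall over 9 weeks in both arms, i.e. 10/9 = 1.11 points per week. SD 10. Non-completers follow the same mean path as everyone else. A participant with no session score contributes the pre-intervention score (week 0).

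**1. The plan's own figure.** For the 2 × 3 interaction, λ = f²·N·m/(1−ρ) = 0.04 × 42 × 3/0.5 = 10.08 on 2 and 80 df, with ρ = 0.5 and sphericity assumed. Power is 0.803, so 42 reproduces. It matters here only for the attrition allowance: (50 − 42)/50 = 16%.

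**2. Shortfall per missing participant.** This is the part of the fall that the carried score misses: (9 − carried week) × 1.11.
- Late loss (all sessions attended, questionnaire missing): CFT (9 − 8) × 1.11 = 1.11; CBT (9 − 4) × 1.11 = 5.56.
- Uniform loss (last contact equally likely at weeks 1–8): mean carried week in CFT is 4.5, shortfall 5.00. In CBT, weeks 1–3 give baseline and weeks 4–8 give week 4, so the mean carried week is (5/8) × 4 = 2.5, shortfall 7.22.

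**3. Bias in the post-treatment arm difference.** Bias towards CFT = (CBT missing rate × CBT shortfall) − (CFT missing rate × CFT shortfall).

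| Missing CFT / CBT | Late loss | Uniform loss |
|---|---|---|
| 16% / 16% | 0.16 × (5.56 − 1.11) = 0.71 | 0.16 × (7.22 − 5.00) = 0.36 |
| 30% / 30% | 0.30 × 4.44 = 1.33 | 0.30 × 2.22 = 0.67 |
| 10% / 30% | 1.67 − 0.11 = 1.56 | 2.17 − 0.50 = 1.67 |
| 30% / 10% | 0.56 − 0.33 = 0.22 | 0.72 − 1.50 = −0.78 |

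**4. Separating the schedule from ordinary carry-forward.** Had both arms given weekly scores, carry-forward would still give (CBT rate − CFT rate) × CFT shortfall. At 10% / 30% that is 0.20 × 5.00 = 1.00 of the 1.67 under uniform loss, and 0.20 × 1.11 = 0.22 of the 1.56 under late loss. The unequal schedule accounts for the rest: 0.67 and 1.33.

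**5. A second reversal.** If CFT non-completers are last seen at session 2 while CBT non-completers supply week 4, at 16% missing in each arm the bias is 0.16 × (2 − 4) × 1.11 = −0.36, against CFT.

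**6. Shape of the fall.** With a front-loaded path reaching 10 points by week 8, fall by week w = 10 × (1 − e^(−w/3))/(1 − e^(−8/3)), week 4 already has 7.91 points. Late loss then gives 2.09 per missing pair: 0.33 at 16% and 0.63 at 30%. Uniform loss gives 0.42 and 0.79. The order of size is unchanged.

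**The case against.** The strongest defence is about size. At 16% missing per arm, the only allowance that the article implies, the bias is 0.04–0.07 SD. Assuming 25 per arm and a pre–post correlation of 0.6, the standard error of the difference in change is 10 × √(2 × 0.4) × √(2/25) = 2.5 points. Simulated comparisons of change scores under these assumptions, with loss spread over sessions 1–8 or 5–8, gave false-positive rates of 4.9–5.5% at 16% and 5.8–6.5% at 30% in both arms. The rate reached 9–11% only at 10% / 30%. If every loss comes after session 8, a check run of 20,000 replicates gave 6.0% at 16% and 8.9% at 30%. The trial also aims only at preliminary efficacy. This argument stands and limits the severity.

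A second defence is that the effect on the stated test is not shown. The figures concern the post-treatment mean difference, whereas the planned ANOVA uses three time points. The article does not say how someone with a filled-in post score and no 3-month score enters it. That also stands.

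A reader might infer that the rule always favours CFT when both arms improve. The documents do not support this. CFT asks for eight appointments and CBT for one, so heavier or earlier loss in CFT cannot be excluded, and the sign can then reverse. A reader might also infer that therapists administer the session BDI. The text places completion at therapist sessions, but the BDI-II is a self-report measure and nothing says who administers it.

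Neither defence justifies the rule itself. It is a stated commitment, not detail left to an unseen analysis plan, and its bias depends on arm-specific contact schedules and dropout.

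**Conclusion.** The concern holds in a conditional form. The rule fills the primary outcome from time points that differ by arm. It produces a spurious CFT advantage if both arms improve and dropout is similar in amount and timing, or greater in CBT. It can work against CFT if CFT loses clearly more participants or loses them before week 4.

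Under the assumed linear fall, the size is about 0.4–0.7 BDI points at 16% missing per arm and 0.7–1.3 at 30%. It is 1.6–1.7 towards CFT at 10% / 30%, and about 0.8 against CFT at 30% / 10% with uniform loss. It would be tempting to attribute the whole 1.6–1.7 to the BDI schedule, but part of it is ordinary carry-forward bias from unequal attrition. All trajectories and dropout rates are assumptions, so the figures illustrate and do not predict. How much the standard errors are understated by treating filled-in values as observed was not computed.

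This should be fixed, but it is not critical to the trial.

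**What to change.** Remove carry-forward from the primary analysis. Analyse the observed pre, post and 3-month BDI-II scores of all randomised participants in a likelihood-based repeated-measures model with condition, time and their interaction, or use multiple imputation by arm. The week-4 score, which both arms supply, may serve as auxiliary information. Either method meets the article's aims of using the available data and analysing by intention to treat, and either also deals with missing 3-month scores. Carry-forward can stay as a labelled sensitivity analysis.

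The cost is a rewritten sentence and slightly more analysis work. The other seven CFT session scores would not enter the primary model. The result would rest on missingness being explained by the data in the model, which the report should state. No additional data collection is needed.
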